## DISCUSSION

4

The persistent increased gap in the rate of hospital admissions and premature mortality rates for people living with diabetes is well documented. Fundamental to achieving good glycaemic control and reduced diabetes associated micro‐ and macrovascular complications is internationally recommended DSME. Existing literature provides evidence that DSME improves quality of life, self‐management skills and short term HbA1c, but persuasive evidence that DSME impacts hospital admissions or premature mortality for people living with type 2 diabetes is lacking.

Heterogeneity of DSME programmes make comparison challenging.^38^, ^39^, ^40^, ^41^ Although accreditation and regulation of DSME programmes is considered as good practice it is not compulsory and differences in the mode, session content, duration and quality assurance of programmes are common. This study will not examine the heterogeneity of different DSME programmes. All programmes reported using relevant Med Code ID codes (presented in Table 1) will be included. Further studies will be required to examine the relationship between DSME variance and outcomes.

Existing UK practice for DSME makes retrospective cohort studies such as ours challenging. DSME attendance is defined as having engaged with 10% of a course's content and completion is defined as having engaged with 60% of a programme's content,^42^, ^43^, ^44^ despite evidence of benefit largely being derived from 100% engagement. Whilst we recognise limitations this poses for retrospective cohort analysis, as this is the nationally accepted coding and reporting model for DSME engagement, and as we are unable to presume missingness of data for DSME attendance in medical records, the existing model will be utilised to determine ‘ever’ and matched ‘never’ cohorts. Secondary analysis will examine differences between attended and completed codes. Further studies are required to analyse the impact of these nationally adopted metrics, which is beyond the scope of this study but is being examined elsewhere.^42^

This study addresses an important gap in the literature using a large real‐world dataset, representative of the general population, linked to HES APC, ONS death registrations, patient level IMD and ethnicity datasets. The design overcomes many of the limitations of previous studies and its scale and matching of patients at baseline allows us to examine the impact of attending DSME on all‐cause and cause‐specific hospital admissions and mortality in people with type 2 diabetes.

### Limitations, generalisability and interpretation

4.1

The medical data available in CPRD are collected during clinical consultations rather than for research, thus the data may be limited by recording quality, and there may be variation in the consistency and accuracy of reporting and coding by GPs. This may introduce inaccuracy into the study findings.

Although CPRD data on diabetes diagnosis has a high level of completeness, not all patient groups or GP practices are captured, for example, private patients, prisoners or some residential home patients. Moreover, some patients chose to opt out of CPRD, and some are exception‐reported by GPs. Furthermore, CPRD data capture may be less complete for ethnicity and socio‐economic demographic data, but this can be largely overcome by data linkage.

This study is observational by nature and reverse causality cannot be excluded as a possible explanation for associations or inferences. We are reliant on the accuracy of ICD‐10 codes and SNOMED‐CT codes to define outcomes. These limitations may introduce bias to the study and will be fully acknowledged in the discussion. Although we will match groups at baseline and manage confounding a priori, potential residual confounding can never be completely eliminated, and causality would need to be confirmed in a randomised controlled trial.

This study has the potential to benefit patients by informing guidelines and clinical strategies for people living with type 2 diabetes.

## ETHICS STATEMENT

CPRD collects anonymised patient data from a network of GP practices across the United Kingdom which are linked to other health related data to provide a longitudinal, representative UK population health dataset. CPRD research data services are delivered by the UK Medicines and Healthcare products Regulatory Agency (MHRA) with support from the National Institute for Health and Care Research. Protocol approval was granted by CPRD (24_003744). Individual patient level consent was not required for this study as all data are deidentified.

### PEER REVIEW

The peer review history for this article is available at https://www.webofscience.com/api/gateway/wos/peer‐review/10.1111/dom.16257.

## Data Availability

Data sharing not applicable to this article as no datasets were generated or analysed during the writing of this protocol.

## APPENDIX A

**TABLE A1 dom16257-tbl-0003:** ICD‐10 codes for each underlying cause of hospitalisation and cause groupings [1].

Underlying causes	ICD‐10 Codes	Tier 1 cause groupings	Tier 2 Cause groupings
Malignant neoplasm of liver and intrahepatic bile ducts	C22	Cancers	DM‐related cancers
Malignant neoplasm of colon, rectosigmoid junction and rectum (i.e. colorectal)	C18, C19, C20	Cancers	DM‐related cancers
Malignant neoplasms of digestive organs except liver and intrahepatic bile ducts or colorectal	C15–C17, C21, C24, C26	Cancers	All other cancers
Malignant neoplasm of gallbladder	C23	Cancers	DM‐related cancers
Malignant neoplasm of pancreas	C25	Cancers	DM‐related cancers
Malignant neoplasms of lymphoid, haematopoietic and related tissue	C81–C96	Cancers	All other cancers
Malignant neoplasm of trachea, bronchus and lung	C33–C34	Cancers	All other cancers
Malignant neoplasm of prostate	C61	Cancers	All other cancers
Malignant neoplasm of breast	C50	Cancers	DM‐related cancers
Malignant neoplasm of cervix	C53	Cancers	All other cancers
Malignant neoplasm of corpus uteri	C54	Cancers	DM‐related cancers
All other neoplasms	C00–C14, C27–C32, C35–C49, C51–C52, C55–C60, C62–C80, C97–D48	Cancers	All other cancers
Respiratory	J00–J98, J19, J22–J99	Respiratory, renal & liver	Respiratory
Respiratory infection	J12–J18, J09–J12, J20–21, A15–A19	Infections	Respiratory infection
Diabetes	E10–E14, excluding E10.0, E10.1, E11.0, E11.1, E12.0, E12.1, E13.0, E13.1, E14.0, E14.1	Diabetes	Diabetes
Acute Myocardial Infarction	I21–I22	Vascular	Acute myocardial infarction
Other ischaemic heart disease & heart failure	I20, I23–I25, I50	Vascular	Ischaemic heart disease
Stroke (cerebrovascular)	I60–I69	Vascular	Stroke
Major Lower limb amputations	OPCS codes: 093–095, 098–099	Amputations	Major amputations
Minor lower limb Amputations	OPCS codes: 101, 104, 108–109, 111–112, 118–119	Amputations	Minor amputations
Hyperglycaemic crisis	E10.0, E10.1, E11.0, E11.1, E12.0, E12.1, E13.0, E13.1, E14.0, E14.1	Diabetes	Hyperglycaemic crisis
Renal disease	N00–N09, N12–N14, N17, N19–N28	Respiratory, renal & liver	Renal disease
ESRD	N18	Respiratory, renal & liver	Renal disease
Kidney infection	N10–11, N15–N16, N30, N39	Infections	Kidney infection
Liver disease	K70–77	Respiratory, renal & liver	Liver disease
Skin, soft tissue and bone infections	L03, L97, I96, M86, B35–49	Amputations	Skin and bone infections
Sepsis	A40–A41	Sepsis	Sepsis

^1^
Pearson‐Stuttard J, Cheng YJ, Bennett J, *et al*. Trends in leading causes of hospitalisation of adults with diabetes in England from 2003 to 2018: an epidemiological analysis of linked primary care records. *Lancet Diabetes Endocrinol*. 2022;10. DOI: 10.1016/S2213‐8587(21)00288‐6.

**TABLE A2 dom16257-tbl-0004:** ICD‐10 codes for each underlying cause of mortality and cause groupings [1].

Underlying causes	ICD‐10 Codes	Tier 1 cause groupings	Tier 2 Cause groupings
Malignant neoplasm of liver and intrahepatic bile ducts	C22	Cancers	DM‐related cancers
Malignant neoplasm of colon, rectosigmoid junction and rectum (i.e. colorectal)	C18, C19, C20	Cancers	DM‐related cancers
Malignant neoplasms of digestive organs except liver and intrahepatic bile ducts or colorectal	C15–C17, C21, C24, C26	Cancers	All other cancers
Malignant neoplasm of gallbladder	C23	Cancers	DM‐related cancers
Malignant neoplasm of pancreas	C25	Cancers	DM‐related cancers
Malignant neoplasms of lymphoid, haematopoietic and related tissue	C81–C96	Cancers	All other cancers
Malignant neoplasm of trachea, bronchus and lung	C33–C34	Cancers	All other cancers
Malignant neoplasm of prostate	C61	Cancers	All other cancers
Malignant neoplasm of breast	C50	Cancers	DM‐related cancers
Malignant neoplasm of cervix	C53	Cancers	All other cancers
Malignant neoplasm of corpus uteri	C54	Cancers	DM‐related cancers
All other neoplasms	C00–C14, C27–C32, C35–C49, C51–C52, C55–C60, C62–C80, C97–D48	Cancers	All other cancers
Respiratory	J00–J99	Other	Respiratory
Diabetes	E10–E14	Other	Diabetes
Ischaemic Heart Disease	I20–I25	Vascular	Ischaemic heart disease
Stroke (cerebrovascular)	I60–I69	Vascular	Stroke
Other circulatory	I00–I19, I26–I59, I70–I99	Vascular	Other circulatory
Renal disease	N00–N28	Other	Renal disease
Liver disease	K70–77	Other	Liver disease
Intentional injury – assault	X85–Y09, Y871	Other	Accidents
Intentional Injury – self harm	X60–X84, Y870	Other	Accidents
Intentional Injury – other intentional injury	Y35, Y36	Other	Accidents
Unintentional injury	V01–X59, Y40–Y86, Y88, Y89	Other	Accidents
Dementia and Alzheimer's	F00–F03, G30	Other	Dementia
All other ICD codes		Other	Other

^1^
Pearson‐Stuttard J, Bennett J, Cheng YJ, *et al*. Trends in predominant causes of death in individuals with and without diabetes in England from 2001 to 2018: an epidemiological analysis of linked primary care records. *Lancet Diabetes Endocrinol*. 2021;9. DOI: 10.1016/S2213‐8587(20)30431‐9.

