**FIGURE 1 dom16257-fig-0001:**
[figure not shown]
Stitching of data and linkage of datasets.^35^, ^36^

Following data linkage to the HES APC dataset, ICD codes for 17 cause‐specific mutually exclusive admission clusters (Appendix 1) will be extracted as identified in a recent epidemiological analysis for people with diabetes in England^11^: ischaemic heart disease, stroke, acute myocardial infarction (MI), diabetes‐related cancers, non‐diabetes related cancers, hyperglycaemic crisis, major amputations, minor amputations, skin and bone infections, respiratory infections, kidney infections, sepsis, respiratory disease (non‐infectious, non‐cancerous), renal disease, chronic kidney disease, liver disease.

More than 50% of deaths in the United Kingdom do not occur in hospital, with ONS mortality data considered the gold standard for mortality records.^33^ Following data linkage with the ONS national death registry, cause‐specific mortality across 12 mutually exclusive clusters (Appendix 2) will be extracted as identified in a recent epidemiological study identifying causes of death in patients with diabetes in England^34^: ischaemic heart disease, stroke, other circulatory, other cancer, diabetes‐related cancer, dementia, diabetes, liver, renal, respiratory, other, injuries. In line with current reconciling guidelines date of death and cause of death will be taken from CPRD to enable linkage for the 25.11% of patients in England that are ineligible for linkage with ONS.^33^

The following recommendations will be applied when linking data from CPRD to ONS mortality data.^33^
If only CPRD date of death is present, this can be used as a reliable piece of information and has been previously validated.If only ONS mortality information is present, its date and causes of death can be used if the linkage rank is ≤2 (Table 2) and the date of death is within the linkage period being examined.If both CPRD and ONS dates of death are available, ONS will be used for the date of death and cause of death when the match rank is ≤2 and the date of death is within the linkage period being examined.If both CPRD and ONS are present and ONS date of death is outside the linkage period, or the match is ≥3 the CPRD date will be used to validate ONS. If the dates coincide ONS date of death and cause of death can be used. If not only CPRD date will be used.

**TABLE 2 dom16257-tbl-0002:** National Health Service (NHS) digital 8‐step linkage algorithm.^33^

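### Table A1 codes the Respiratory admission cluster to include every J code of Respiratory infection, against the stated exclusivity, and the text and table list different sets of 16 clusters where 17 are stated

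*Protocol article*

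**What the plan says.** Section 3.4 (Data processing and analysis, the text after Figure 1) states that "ICD codes for 17 cause‐specific mutually exclusive admission clusters (Appendix 1) will be extracted". The list that follows names the clusters and ends with "respiratory disease (non‐infectious, non‐cancerous), renal disease, chronic kidney disease, liver disease". So the respiratory cluster is meant to exclude infections, and chronic kidney disease is meant to stand apart from renal disease.

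Table A1 in Appendix A supplies the codes:

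- Respiratory: "J00–J98, J19, J22–J99".
- Respiratory infection: "J12–J18, J09–J12, J20–21, A15–A19".
- Diabetes, with its own Tier 2 group: "E10–E14, excluding E10.0, E10.1, E11.0, E11.1", followed by the remaining .0 and .1 exclusions.
- N18: a row labelled ESRD, placed in the Tier 2 group Renal disease.

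Objective 2 (Aims and Objectives) covers cause-specific as well as all-cause admissions. Section 3.6 plans rate ratios and time-to-event models comparing the ever and never groups.

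**The concern.** The printed codes contradict two statements in the text: that the clusters do not overlap, and that the respiratory cluster is non-infectious. Table A1 is the working list from which admissions will be extracted, so an analyst who follows it literally will assign one influenza or pneumonia admission to two outcomes. The cluster reported as non-infectious would then contain every J-coded infection that Respiratory infection contains. An association confined to infections would appear under both headings and could be read as two separate findings.

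The disagreement over the list of clusters is a second, independent problem. The number of cause-specific admission outcomes is given as 17, but neither the text nor the table reaches it. A reader cannot tell whether diabetes admissions without hyperglycaemic crisis are an outcome, or whether N18 is analysed separately.

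**Working it through.** **1. Overlap of codes.** Each ICD-10 range in Table A1 was expanded to three-character positions, and every pair of groups was intersected. The diabetes rows, which use four-character exclusions, and the OPCS rows were read by eye.

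- Respiratory: J00–J98 gives 99 positions. J19 and J22–J98 already lie inside that range, so the rest of the string adds only J99. Total: 99 + 1 = 100, which is all of J00–J99.
- Respiratory infection, J codes: J09–J12 (4) + J12–J18 (7) − J12 listed twice (1) + J20 and J21 (2) = 12. Adding A15–A19 (5) gives 17.
- Intersection: J09, J10, J11, J12, J13, J14, J15, J16, J17, J18, J20 and J21, which is 12 of 12 J codes. Only A15–A19 is unique to the infection cluster.
- No other pair of ICD groups in Table A1 shares a code.

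**2. Test of the likely correction.** Most of the printed string is redundant, which suggests that the first range was meant to stop earlier. If it ends at J08, Respiratory has J00–J08 (9) + J19 (1) + J22–J99 (78) = 88 positions. Then 88 + 12 = 100, the overlap is zero, and the two clusters cover J00–J99 exactly once. This does not make the cluster non-infectious, because the acute respiratory infection codes J00–J06 and J22 stay in it.

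**3. Count of clusters.** The stated figure of 17 is not reproduced from either list.

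| | Count | Not in the other list |
|---|---|---|
| Named in Section 3.4 | 16 | chronic kidney disease |
| Tier 2 groups in Table A1 | 16 | Diabetes |
| In both | 15 | – |
| Union | 15 + 1 + 1 = 17 | – |

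For comparison, the mortality list agrees with itself: 12 stated, 12 named in the text and 12 Tier 2 groups in Table A2. Table A2 has a single respiratory row (J00–J99), so no overlap arises there.

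**4. Effect on the rate ratio.** Let s be the share of infections among admissions in the J00–J99 cluster in the never group, and let RRi and RRn be the rate ratios for infectious and non-infectious disease. The cluster as printed then estimates

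RR = s × RRi + (1 − s) × RRn.

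The documents give none of these three quantities. As an assumption only, take RRi = 0.8, RRn = 1.0 and s from 0.3 to 0.6:

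- s = 0.3: 0.3 × 0.8 + 0.7 × 1.0 = 0.94
- s = 0.6: 0.6 × 0.8 + 0.4 × 1.0 = 0.88

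Under these values a null effect on non-infectious disease would read as a 6% to 12% reduction. If RRi = RRn, the ratio is not shifted at all.

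**The case against.** The strongest reply is that this is a misprint in one string. On that view, the promise of mutually exclusive clusters already obliges the analyst to assign each admission once. The hypotheses concern all-cause admissions and mortality, and Section 3.5 calls the proportion hospitalised the main outcome; neither uses the clusters. An error in reading the PDF cannot be wholly excluded for a single digit either.

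Much of this stands as a limit on scope: one pair of cause-specific outcomes is affected, and the main results are not. It does not dispose of the point. Single assignment needs a rule for choosing between the two clusters, and the printed codes put all 12 J codes in both. A misread digit also cannot explain why text and table list different clusters.

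A second reply is that 17 may be correct, with one name dropped from the text and N18 merged under a neighbouring Tier 2 label. That is plausible, since the union is exactly 17. The number need not change, but the two lists still have to be reconciled.

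A reader might also infer that the respiratory rate ratio is inflated 1.4- to 2.5-fold. That factor is 1/(1 − s) for s between 0.3 and 0.6. It describes an absolute rate under an assumed share. The planned comparison is between ever and never groups coded alike, so the ratio is blended and not multiplied. Nor do the documents show that infections would dominate the cluster; that would need s above 0.5.

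**Conclusion.** The point holds for the admission code list. As printed, the Respiratory cluster is neither exclusive of Respiratory infection nor non-infectious: 12 three-character codes are shared, and these are all the J codes of the infection cluster. The text and Table A1 each give 16 clusters against a stated 17, and they differ in one cluster each. The size of any distortion in the rate ratio cannot be fixed from the document, because it depends on the infection share and on how far the two effects differ. That J08 is the intended end of the first range is an inference from the redundant string and the exact partition it produces; the source list is not at hand.

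Some wider readings are tempting but not supported:

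- **Mortality results are wrong.** Table A2 has no such overlap, and its 12 groups match the text.
- **Heart failure is misplaced.** Table A1 puts I50 with ischaemic heart disease, while for deaths it falls in "I00–I19, I26–I59, I70–I99". The row label in Table A1 names heart failure openly, the two tables are taken from different source analyses, and no objective compares the two results. This is a choice and not an error.
- **Amputation rows break exclusivity.** They use OPCS codes, so a precedence rule is needed, but such a rule is commonly left to a fuller plan.
- **COVID-19 has no category.** Mutually exclusive does not mean exhaustive. Unclustered admissions still count as all-cause, and Table A2 sends unlisted causes of death to Other.

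**What to change.** Before extraction:

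1. Check the Respiratory string in Table A1 against the source list and correct the first range. If J00–J08 is confirmed, the entry becomes J00–J08, J19, J22–J99 and the overlap disappears.
2. Then either move the remaining acute respiratory infection codes (J00–J06 and J22) to Respiratory infection, or drop the non-infectious label in Section 3.4.
3. Make Section 3.4 and Table A1 list the same clusters. One way is to add Diabetes to the text and keep N18 as its own Tier 2 group, under one name in both places (the text says chronic kidney disease, the table ESRD). That gives the stated 17. If a different set is intended, state the number that matches it.
4. Rerun the pairwise intersection on the final code list to confirm that no ICD code falls in two clusters.

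The cost is an edit to the code list and one sentence of text. No new data and no change to the planned models are needed.

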In studies examining the impact of DSME on mortality, most (*n* = 28) cite mortality as a reason for drop‐out rather than examining mortality as a primary outcome measure,^13^, ^16^, ^17^, ^18^ and only two studies report significant improvements following DSME.^13^, ^16^ In a study from Hong Kong, attending one or more DSME sessions was associated with lower all‐cause mortality (HR:0.59, CI 95% 0.632–0.968, *p* = 0.024); however, differences existed between study groups,^13^ with similar findings described in a UK randomised control trial, where mortality in participants requiring ambulance transfer for severe hypoglycaemia was 33.3% in those that had attended DSME compared with 51.2% in those receiving standard care without DSME (HR 0.65, *p* = 0.025).^16^ DSME workshops for an elderly Argentinian type 2 cohort resulted in an 33% lower 6‐year crude mortality rate, but significance was lost in multivariate analysis showing only a weak (18%) association between DSME attendance and reduced mortality (HR 0.82; 95%CI: 0.61–1.08) but socio‐economic data was not reported as a confounder, and those in the non‐attendance group had an increased stroke prevalence, higher diastolic blood pressure and LDL‐C which could explain the increased mortality rate.^17^ This weak association between DSME attendance and mortality was also reported in an earlier study which simulated the long‐term cost‐effectiveness of DSME interventions over 20 years, however, results obtained in this simulated RCT may not be representative of diabetes care delivered outside of this type of clinical trial.^18^

In short, existing studies provide evidence that DSME improves well‐being, self‐management skills and short‐term blood sugar control (HbA1c), but crucially evidence of an impact of DSME on hospital admissions and premature mortality is limited and conflicting and has not been assessed in a real world setting on this scale.

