### Data selection

3.3

To minimise the impact of incorrect information or flawed subject selection the ‘*ever’* cohort will be matched at baseline to patients who have ‘*never’* received DSME (*n* = 584 312). Age,^22^, ^23^ age at diagnosis and diabetes duration^22^, ^24^, ^25^, ^26^ are the most important predictors of one‐year mortality in type 2 diabetes.^27^ Every decade of earlier diabetes diagnosis is associated with 3–4 years of lower life expectancy.^24^

Cohort analysis, systematic review and meta‐analysis have considered the association between diabetes and sex, demonstrating that women generally have a higher risk of coronary heart disease and all‐cause mortality (58%) compared to men and a 13%–17% greater risk of all‐cause mortality.^28^, ^29^ Moreover, the additional likelihood of developing cancer and the higher risk of premature mortality from having diabetes is more pronounced in women.^30^

Patients will therefore be matched at baseline for age ± 5 years, age at diagnosis ±5 years, diabetes duration ±1 year and sex who are present in the dataset from the same start year or earlier.

This study will adopt an intention‐to‐treat analysis, with patients contributing only to the original exposure group in which they have been assigned, irrespective of when they receive DSME. Baseline for the ‘ever’ group and their matched controls will be the date of DSME intervention. Patients will remain exposed until they are censored by death, leave the GP practice, leave a GP practice which contributes to CPRD data or end of the study period (29 March 2021).

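### Tables A1 and A2 apply cause groupings built on data to 2018 to follow-up ending in March 2021, with no COVID-19 category

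*Protocol article*

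**What the plan says.** Section 2 makes cause-specific admissions and cause-specific mortality objectives alongside the all-cause outcomes, and section 3.6 plans tests and models for them.

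Section 3.4 defines the admission outcomes as "17 cause‐specific mutually exclusive admission clusters", with codes in Table A1, and the deaths as 12 clusters, with codes in Table A2. The references under the two tables cover 2003 to 2018 (admissions) and 2001 to 2018 (deaths). Section 3.3 continues follow-up to the "end of the study period (29 March 2021").

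The rows that matter here are:

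- Table A1, 'Respiratory infection': "J12–J18, J09–J12, J20–21, A15–A19".
- Table A1, 'Respiratory': "J00–J98, J19, J22–J99".
- Table A1, 'Hyperglycaemic crisis': "E10.0, E10.1, E11.0, E11.1, E12.0, E12.1, E13.0, E13.1, E14.0, E14.1".
- Table A1, 'Diabetes': "E10–E14, excluding E10.0, E10.1, E11.0, E11.1", with the other '.0' and '.1' codes excluded in the same way.
- Table A2, 'Respiratory': J00–J99. Its last row is "All other ICD codes", grouped as 'Other'.

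Hypoglycaemia appears only in section 1, as the setting of a cited trial in "participants requiring ambulance transfer for severe hypoglycaemia".

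**The concern.** A grouping developed on data to 2018 could not provide for COVID-19. Carried unchanged to March 2021, it leaves COVID-19 to fall wherever the old ranges happen to put it. 'Respiratory infection' will be read as covering respiratory infection throughout follow-up, but for the last year it would leave out admissions given a COVID-19 code as primary cause. An association between DSME and COVID-19 mortality would appear in the residual death category, where no reader would look for it.

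There is a smaller question about acute metabolic admissions. Table A1 has no row from which hypoglycaemia can be identified, and the label 'Hyperglycaemic crisis' is attached to every '.0' code of E10–E14. Whether the label fits depends on what those codes contain, which the protocol does not print.

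**Working it through.** **1. Code coverage of Table A1.** Each of the 27 rows was expanded to three-character codes and the relevant codes were looked up.

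| Code | Table A1 row(s) |
|---|---|
| U07 to U10 | none |
| B34, B97 | none |
| J12 | 'Respiratory' and 'Respiratory infection' |
| E16 | none |
| E10–E14, '.0' and '.1' | 'Hyperglycaemic crisis' |
| E10–E14, all other subdivisions | 'Diabetes' |

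No U code appears anywhere in the table, and the only E codes are E10–E14. The cluster list in section 3.4 names neither COVID-19 nor hypoglycaemia.

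**2. Where a COVID-19 event goes.** The premise is that COVID-19 is coded at U07.1 or U07.2; the protocol does not say so.

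- Admission, U code primary: no cluster.
- Admission, J12 primary: counted as 'Respiratory infection', and as printed also as 'Respiratory'.
- Death, U code underlying: outside J00–J99, so it takes the residual row and becomes 'Other'. In the Tier 1 grouping 'Respiratory' is itself under 'Other', so the misplacement shows only at Tier 2, the level of the 12 clusters in section 3.4.

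**3. Calendar extent.**

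- Study window, 29 March 2011 to 29 March 2021: 10 × 365 + 3 leap days = 3653 days.
- End of the code sources to end of follow-up, 1 January 2019 to 29 March 2021: 365 + 366 + 87 = 818 days; 818 / 365.25 = 2.24 years.
- Time removed by a cut-off of 29 February 2020: 365 days to 28 February 2021 plus 29 = 394 days; 394 / 365.25 = 1.08 years; 394 / 3653 = 10.8% of the window.

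The 10.8% is a share of calendar time. In an open cohort the share of person-time or events may differ, and the protocol gives no counts from which to work it out.

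**4. What is not touched.** All-cause admissions and deaths do not use the cause tables. Sepsis (A40–A41), kidney infection (N10–N11, N15–N16, N30, N39) and skin and bone infection (L03, L97, I96, M86, B35–B49) keep their definitions.

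**5. The '.0' codes.** No event counts or shares are given, so the size of any mislabelling cannot be computed. It is zero if the '.0' codes contain no hypoglycaemic coma, and otherwise an unknown share of the cluster.

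**The case against.** The strongest case on the other side has four parts.

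- **All-cause outcomes carry the stated hypothesis and include every COVID-19 event.** This stands. It limits the concern to the cause-specific results.
- **A residual category exists to receive unlisted causes, and COVID-19 pneumonia coded to J12 is still counted.** Both are true. The point therefore covers only U-coded events, in about the last year. But a residual that absorbs a new respiratory infection makes both 'Respiratory' and 'Other' harder to interpret, and admissions have no such residual.
- **Matched controls take the DSME date as baseline (section 3.3), so both groups start at the same calendar time.** This also stands. The omission is not shown to bias ever against never; it changes what the outcomes measure.
- **Table A1 follows a published grouping.** Comparability has value, but that grouping's source period ends before the pandemic.

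Several stronger readings are tempting and not supported. A reader might infer that Table A1 is wrong because it lacks the residual row found in Table A2. Section 3.4 calls the admission clusters mutually exclusive, not exhaustive, and nowhere says that they should sum to all-cause admissions. A reader might infer that the infection outcomes as a whole mislead; three of the four infection-type clusters are unaffected by this gap. A reader might also infer that severe hypoglycaemia is being counted as its opposite. That depends on the content of the '.0' codes, which the documents do not give. Hypoglycaemia coded elsewhere in E10–E14 would enter 'Diabetes', though not identifiably. The trial cited in section 1 used severe hypoglycaemia to define its participants and reported mortality, so it does not make hypoglycaemia a required outcome here.

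**Conclusion.** The COVID-19 point holds. Both cause tables are used about 2.2 years beyond the end of their sources without adaptation. U-coded COVID-19 admissions enter no cluster, and U-coded deaths go to 'Other'. The effect is confined to cause-specific results, chiefly 'Respiratory infection' admissions and the 'Respiratory' and 'Other' death clusters, over about the last 1.1 calendar years. This rests on one premise from outside the protocol, that COVID-19 is coded at U07.1 and U07.2, which the sponsor can confirm at once. The number of events affected is unknown.

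The hypoglycaemia point is secondary and conditional. It is certain that E16 is in no row and that no Table A1 category identifies hypoglycaemia. Whether 'Hyperglycaemic crisis' is mislabelled depends on a check against ICD-10. No distortion of the rate ratio can be quoted, because the share of such events and any difference in effect would both have to be invented.

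**What to change.** 1. Add a COVID-19 row (U07.1, U07.2, confirmed against the ICD-10 edition used in the linked data) to Tables A1 and A2, and to the cluster lists in section 3.4.
2. Repeat the main models with follow-up ended on 29 February 2020 as a sensitivity analysis.
3. Check the '.0' codes of E10–E14 against ICD-10. If they include hypoglycaemic coma, report E16 admissions separately and run 'Hyperglycaemic crisis' with and without the '.0' codes.

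While the tables are open, two matters in the same place should be reconciled. J09–J18 and J20–J21 fall in both respiratory rows although the clusters are called mutually exclusive, and this decides where J12 pneumonia is counted. Section 3.4 states 17 admission clusters but lists 16.

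The cost is a code-list edit before extraction and one further run of the main models. The small downside is one more cause-specific outcome per table, at the 5% level set in section 3.6, and a departure from the published grouping. That departure can be bridged by also showing the results under the published groups. Step 3 adds an E16 outcome and one repeat of a single cluster, and only if the check calls for them.
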